# Combined extracorporeal shock wave lithotripsy and endoscopic treatment for pain in chronic pancreatitis (SCHOKE trial): study protocol for a randomized, sham-controlled trial

**DOI:** 10.1186/s13063-020-04296-0

**Published:** 2020-04-16

## Abstract

**Background:**

Pain is the primary symptom of chronic pancreatitis (CP) and remains a considerable therapeutic challenge. In patients with obstruction of the pancreatic duct, including stones and strictures, endoscopic treatment with or without preceding extracorporeal shock wave lithotripsy (ESWL) has been used for pancreatic duct decompression. The rationale for these procedures is based on the assumption that obstruction of the pancreatic duct leads to ductal hypertension and pain. However, clinical pain symptoms correlate poorly with pancreatic duct morphology, and the evidence for pancreatic duct decompression as an effective treatment for pain is based on case series and comparison between different procedures. No randomized, prospective, sham-controlled trials are currently available. The SCHOKE (Extracorporeal Shock Wave Lithotripsy and Endotherapy for Pain in Chronic Pancreatitis) trial is a randomized, sham-controlled trial designed to determine if pancreatic duct decompression is an effective treatment for pain in patients with CP.

**Methods:**

The SCHOKE trial is a randomized, single-blind, parallel-group, sham-controlled trial designed to evaluate the effect of combined ESWL and endoscopic treatment for pain in patients with CP. In total, 106 adult patients with painful CP and pancreatic duct obstruction will be randomized to combined ESWL and subsequent endoscopic treatment or corresponding sham procedures. The primary outcome is pain relief during the 3-month postrandomization period as documented in a pain diary. Secondary outcomes include quality of life and functional scores, patient global impression of change, change in use of analgesics, frequency of hospitalization, and complications. Standard follow-up is at 3 and 6 months after randomization. In an experimental substudy, quantitative sensory testing obtained before and after intervention will be used to obtain information on central pain processing and to develop models for prediction of treatment outcome.

**Discussion:**

The SCHOKE trial investigates if pancreatic duct decompression, obtained by combined ESWL and endoscopic treatment, is effective for pain treatment in patients with CP.

**Trial registration:**

ClinicalTrials.gov, NCT03966781. Registered on May 25, 2019.

**Protocol date and version identifier:** March 1, 2020; version 3.0.

**Sponsor:** [name], Department of Medical Gastroenterology, Asian Institute of Gastroenterology, Hyderabad, Telangana, India.

## Introduction

Pain is the primary symptom of chronic pancreatitis (CP) and remains a considerable therapeutic challenge [1]. In patients with pathological changes of the pancreatic duct, including stones and strictures, endoscopic treatment with or without preceding extracorporeal shock wave lithotripsy (ESWL) and surgery has been used with varying success to treat pain [2–4]. The rationale for such invasive procedures is based on the hypothesis that obstruction of the pancreatic duct leads to ductal hypertension and pain [5, 6]. However, clinical pain symptoms correlate poorly with pancreatic ductal morphology, as assessed by cross-sectional imaging [7, 8], and the response to endoscopic or surgical treatment is unpredictable, with long-term response rates ranging from 30% to 60% [3, 9, 10]. Also, the evidence for these treatments is based on case series and comparison between different procedures; no randomized, prospective, sham-controlled trials have evaluated the effectiveness of invasive treatments for pain in CP [9–11]. Additionally, a marked placebo effect has been observed in most trials of painful CP, and this, together with the natural history of disease, needs consideration when treatment effects are evaluated [12–14]. Therefore, the evidence for invasive treatments for pain in CP can be questioned [14].

Recent meta-analyses have documented that nonspecific effects of invasive procedures are generally large, particularly in the field of pain-related conditions and for endoscopy-based therapies [15, 16]. For example, endoscopic retrograde cholangiopancreatography (ERCP) with sphincterotomy (biliary or pancreatic sphincterotomy or both) has for many years been considered the state-of-the-art treatment for patients with abdominal pain due to suspected sphincter of Oddi dysfunction. However, a high-quality randomized controlled trial (RCT) showed that patients who had no sphincterotomy at ERCP, and who were blinded to their treatment, reported as much pain relief as those who underwent sphincterotomy [17, 18]. These findings challenge conventional wisdom and underscore the necessity for appropriately conducted RCTs to include a sham procedure when the effectiveness of invasive procedures is evaluated [14].

Albeit endoscopic treatment or surgery is widely used for pain in CP, these treatments are only effective in a subset of patients [4, 9, 19, 20]. An improved understanding of the mechanisms underlying pain in CP suggests that the pain etiology in most patients is multifactorial, and, in addition to the proposed mechanisms for pain (ductal obstruction/hypertension), a large body of evidence supports a “neuropathic pain phenotype” with abnormal processing in the peripheral and central neural pathways [6, 21, 22]. Invasive procedures will not be effective in neuropathic pain and can even be considered harmful [14]. This likely explains the variable response to endoscopic and surgical treatments and underlines an unmet need for biomarkers to identify responders to the different treatment modalities.

Quantitative sensory testing (QST) can be used to investigate the state of the pain system. The technique is based on the rationale that different neural pathways and networks can be explored using standardized stimulation with simultaneous recording of the evoked pain response by psychophysical and/or objective methods [23]. Due to spinal convergence between visceral afferents from the pancreas and somatic afferents from the T10 skin dermatome, somatic QST can reliably be used to assess if the pain system is locally sensitized by nociceptive input from the pancreas (segmental sensitization) [24, 25]. However, in many patients with chronic pain, the pain system has become dysfunctional and has undergone widespread sensitization, which is evident as abnormal responses (hyperalgesia) to stimuli applied in areas remote from the pancreas [26]. Taken together, QST profiling based on testing in several dermatomes, together with specific test paradigms (temporal summation and assessment of descending inhibition), can be used to determine whether patients have abnormal central pain processing or evidence of segmental or widespread sensitization [27–29].

## Methods

The study protocol is reported in accordance with the Standard Protocol Items: Recommendations for Interventional Trials (SPIRIT) guidelines (Additional file 1).

### Study hypothesis and aim

The hypothesis of the study is that pancreatic duct decompression following ESWL and endoscopic treatment induces short-term (3 months) and midterm (6 months) pain relief in patients with CP compared with a sham procedure. In addition, we hypothesize that QST can be used to predict the outcome of treatment. Hence, patients with evidence of widespread sensitization of central pain pathways are hypothesized to have a worse outcome after ESWL and endoscopic treatment than patients with no evidence of widespread sensitization.

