### Outcomes

The study consists of a clinical part and an experimental part. The clinical part of the study aims to investigate the pain-relieving effects of combined ESWL and endoscopic treatment in patients with painful CP in comparison with sham treatment. The experimental part of the study aims to evaluate if QST profiles obtained prior to ESWL and endoscopic intervention can be used for prediction of treatment outcome.

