#### Experimental endpoints

The following experimental pain measures will be employed prior to intervention as well as 24–48 h and 3 months after intervention to characterize changes in pain processing induced by the assigned procedures:
Muscle pressure stimulation (pancreatic viscerotome [T10 ventral and dorsal] and control areas [C5, L1 and L4])Bone pressure stimulation (tibia bone)Temporal summation to repetitive pinprick stimulations of the pancreatic area (T10) and control area [dominant forearm])Conditioned pain modulation (CPM)

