### Statistical analysis

The primary analysis of clinical endpoints will be by intention to treat, meaning that all randomized patients are included in their initially assigned study arm, regardless of adherence to the study protocol. Experimental endpoints will be evaluated by per-protocol analysis, meaning that only patients completing the experimental setup will be included. A repeated measures linear mixed effects model will be used for the primary analysis and will include terms for treatment group, assessment time point (week), and the interaction of treatment with assessment time point. Summary statistics of pain scores will be provided for the individual time points, and the difference in pain scores between groups after 3 months is considered the primary efficacy parameter. Subgroup and covariate analyses will be performed if applicable and in case differences in patient subgroups deemed clinically relevant are evident. Subsequent analyses directed at the secondary, experimental, and safety endpoints are analyzed using appropriate statistics, including mixed effect models, Fisher’s exact tests, and Student’s *t* tests or Wilcoxon rank-sum tests as appropriate. The predictive value of the QST profiles will be analyzed using logistic regression models.

We plan to conduct an interim analysis after approximately one-third of patients (*n* = 40) have been randomized and have completed 6 months of follow-up, using a two-sided significance test with the O’Brien–Fleming spending function and a type I error rate of 5%. An independent statistician, blinded to the treatment allocation, will perform the interim analysis. The statistician will report to an independent data and safety monitoring board (DSMB). The DSMB will have unblinded access to all data and will decide on the continuation of the trial and report to the internal review board of the Asian Institute of Gastroenterology. If there is a highly significant difference in improvement in pain in the treatment arm, then all subsequent patients will be subjected to this. The trial will not be stopped in case of futility, unless the DSMB advises otherwise during the course of safety monitoring.

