## Discussion

Pain is the primary symptom of CP and is associated with poor health-related outcomes, including reduced life quality, disability, and increased health resource use [37–39]. Pain treatment is unsatisfactory in a large proportion of patients and generally based on low-quality evidence in particular for invasive treatments (endoscopy and surgery) [14]. The SCHOKE (Extracorporeal Shock Wave Lithotripsy and Endotherapy for Pain in Chronic Pancreatitis) trial is a randomized, sham-controlled trial designed to determine if pancreatic duct decompression is an effective approach for obtaining pain relief in patients with CP. According to current guidelines, invasive procedures are recommended for pain treatment in the context of CP, and some practitioners even advocate for surgical treatment in the early phase of CP [32, 40, 41]. However, neither surgery nor endoscopic therapy has been thoroughly evaluated in sham-controlled trials [14]. The present study will, for the first time, provide sham-controlled evidence for the effectiveness of pancreatic duct decompression as a remedy to relieve pain in CP.

The mechanisms responsible for pain in patients with CP are multifactorial, and thus it is to be expected that no treatment can effectively relieve pain in all patients [42]. Identification of biomarkers that link pain mechanisms with specific treatment modalities is therefore an unmet need in the field, but there are currently few personalized approaches to pain treatment in CP [29]. For example, the presence, severity, and temporal nature of pain correlate poorly with imaging findings, and, as such, imaging can only be used to identify cases in which an invasive treatment is technically feasible, but it cannot be used to determine if patients will benefit from the planned treatment [7, 8, 43]. A QST protocol designed for characterization of pancreatic pain has previously shown effectiveness for the prediction of analgesic outcome in patients with CP and may serve as a useful biomarker for endoscopic treatment efficacy as well [24]. The SCHOKE trial therefore includes a QST testing paradigm specifically developed to assess and characterize pain in CP [29].

In conclusion, the SCHOKE trial is a randomized, sham-controlled trial that investigates whether pancreatic duct decompression is effective for obtaining pain relief in patients with painful CP.

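### The QST hypothesis compares sensitized with non-sensitized patients only after active treatment, so it can show prognosis after decompression but not who benefits from decompression

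*Protocol article*

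**What the plan says.** Study hypothesis and aim contains two hypotheses. The efficacy hypothesis is framed against sham. The QST hypothesis is not. It opens in general terms, "we hypothesize that QST can be used to predict the outcome of treatment", and then becomes specific: patients with widespread sensitization "are hypothesized to have a worse outcome after ESWL and endoscopic treatment than patients with no evidence of widespread sensitization".

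The Outcomes section describes the experimental part in the same way, as an evaluation of whether "QST profiles obtained prior to ESWL and endoscopic intervention can be used for prediction of treatment outcome".

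The intended use is stated elsewhere. The Introduction speaks of an "unmet need for biomarkers to identify responders to the different treatment modalities". The Discussion says that the QST protocol "may serve as a useful biomarker for endoscopic treatment efficacy as well".

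On analysis, the Statistical analysis section gives one sentence: "The predictive value of the QST profiles will be analyzed using logistic regression models". It names no arm, no treatment term and no interaction. The analysis set is also given there: "Experimental endpoints will be evaluated by per-protocol analysis, meaning that only patients completing the experimental setup will be included". According to Experimental endpoints, QST is recorded before and after intervention "to characterize changes in pain processing induced by the assigned procedures", so sham patients should have baseline QST as well.

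**The concern.** A marker is prognostic if patients who carry it do worse whatever they receive. It is predictive of benefit if the difference between active and sham depends on it. A comparison of marker groups that have all been actively treated mixes the two. Sensitized patients may do worse after ESWL and ERCP because they would have done equally worse after sham, with the same gain from decompression as everyone else.

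Identifying responders and marking treatment efficacy are both claims about the active-versus-sham difference. The Introduction itself says that placebo response and natural history have to be taken into account when treatment effects are judged, and the sham arm is there for that purpose. The QST hypothesis as worded does not use it. At stake is the interpretation of the experimental part: a correct finding about prognosis could be presented as evidence that sensitized patients gain less from the procedure.

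**Working it through.** **Inputs from the documents** (Sample size determination): difference 30%, SD 45%, 48 per group, power 90%, two-sided 0.05.

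**Assumptions not in the documents:** 48 patients per arm evaluable for QST; proportion q with widespread sensitization between 30% and 50%; a prognostic shift g, the same in both arms, so that the true treatment-by-marker interaction is zero.

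**The plan's own figure.** n per arm = 2(1.96 + 1.2816)² × 45² / 30² = 47.3, rounded up to 48. Power at 48 per arm is 90.4% by the normal approximation. The figure reproduces. It concerns the primary comparison only; no sample size is stated for the QST hypothesis.

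**Step 1: the contrast as worded (active arm only).** SE = 45 × √(1/(48q) + 1/(48(1−q))). This is 12.99 for q = 50% and 14.17 for q = 30%. The probability of significance is Φ(g/SE − 1.96) + Φ(−g/SE − 1.96).

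| Shift g, same in both arms | q = 30% | q = 50% |
|---|---|---|
| 0 | 5.0% | 5.0% |
| 15 points | 18.5% | 21.1% |
| 22.5 points | 35.5% | 41.0% |
| 30 points | 56.2% | 63.7% |

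**Step 2: the interaction using both arms.** The SE is √2 times larger: 18.37 for q = 50% and 20.05 for q = 30%. With a true interaction of zero, this test rejects in 5% of trials whatever the shift g.

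**Step 3: check on a binary outcome.** The outcome is response, taken as a pain reduction of at least 30%. The mean percent reduction is 10 in sham and 40 in active; half the patients are sensitized; total SD is 45. With shifts of 20, 30 and 36 points in both arms, logistic regression in the active arm is significant in about 25%, 50% and 66% of simulated trials. The upper figure is about 60% if the SD of 45 excludes the marker's own contribution. The linear interaction test rejects in about 5%.

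A second simulation sets response in non-sensitized patients at 65% active and 40% sham, with the same marker odds ratio in both arms. At odds ratios of 0.4, 0.25 and 0.15 the active-arm test is significant in 35%, 64% and 89% of trials, and the logistic interaction test in 2% to 5%.

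**Step 4: what the interaction test can detect.** For a true 30-point difference in benefit, power is Φ(30/20.05 − 1.96) = 32% at q = 30% and Φ(30/18.37 − 1.96) = 37% at q = 50%; simulation at q = 50% gives 36% to 38%. The difference needed for 80% power is (1.96 + 0.8416) × SE, that is 51 points at q = 50% and 56 points at q = 30%.

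**The case against.** The hypothesis is coherent as written. It speaks of outcome after treatment, not of gain over sham, and a contrast among treated patients answers that question. The benefit reading has to be drawn from the Introduction and the Discussion, and the Discussion is hedged. This stands, and it locates the problem: the hypothesis and the stated use do not match, so one of them has to change.

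A reader might infer that the plan excludes the sham arm from the QST analysis. The documents do not support that. The sentence on logistic regression does not restrict the model to one arm, QST is recorded around whichever procedure was assigned, and model terms may sit in an analysis plan that is not shown. The point therefore rests on the wording of the hypothesis. An analysis plan faithful to that wording would test the contrast among treated patients.

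A reader might also take the 20% to 65% as false-positive rates. They are not. In those scenarios sensitized patients truly do worse after active treatment, so a significant result supports the hypothesis as worded. The error arises only if the result is then read as a difference in benefit.

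Finally, a reader might infer that the trial would advise against decompression in sensitized patients. Nothing in the protocol says that QST results will be used in that way, and the abstract describes this part as an experimental substudy.

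**Conclusion.** The point holds in this form: the QST hypothesis can establish prognosis after decompression, while the Introduction and Discussion look to QST as a marker of benefit from it. A purely prognostic marker could be reported as an efficacy biomarker. This conclusion follows from the wording alone. The rates (about 20% to 65% significant in the active arm against 5% for the interaction, for shifts of 15 to 30 points) only illustrate its possible size. They depend on assumed prevalence and shifts and on 48 evaluable patients per arm, and the documents give no information on how sensitized patients fare under sham. The primary comparison and its sample size are unaffected. The change is worth making because the randomized sham arm and its baseline QST should already be available.

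**What to change.** Restate the QST hypothesis as: the active-minus-sham difference in 3-month pain is smaller in patients with widespread sensitization. Declare its test from the start as a prespecified exploratory analysis in both arms, among patients with baseline QST. Choose one model in advance, because an interaction depends on the scale on which it is measured:

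- the stated logistic model, with treatment, QST and treatment-by-QST terms; or
- the stated mixed model, with QST, QST-by-week, QST-by-treatment and QST-by-treatment-by-week added and the contrast taken at 3 months. A single QST-by-treatment term would give an effect modification averaged over the weeks.

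Report the active-minus-sham difference with its 95% CI at each QST level, and label any association within the active arm as prognostic only. The simpler alternative is to keep the present hypothesis and limit the claim throughout to prognosis after treatment.

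Cost: no new data. Power is low, about 32% to 38% for a 30-point difference in benefit, which is as large as the whole effect the trial is sized for, so the result may well be inconclusive and the CI should carry the interpretation. The analysis set for this endpoint changes from patients who complete the experimental setup to all patients with baseline QST. The mixed-model option would also move this analysis from the stated logistic model to a continuous outcome.

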### Study design and setting

We are conducting a randomized, single-blind, single-center, parallel-group, sham-controlled, prospective trial designed to evaluate the effect of combined ESWL and endoscopic treatment for pain in adult patients with CP. The study will be conducted at the tertiary care academic Asian Institute of Gastroenterology in Gachibowli, Hyderabad, India.

### Inclusion criteria

A diagnosis of chronic calcific pancreatitis diagnosed using the Mayo Clinic diagnostic criteria [30]. Both diabetic and nondiabetic patients will be allowed to enter the study.Age ≥ 18 years.Chronic abdominal pain characteristic for CP with a pain intensity > 3 on a 0–10 visual analogue scale (VAS) and meeting the criteria for chronic pain (pain ≥ 3 days per week for ≥ 3 months).Obstruction of the pancreatic duct due to intraductal stones with dilation of the duct proximal to the obstruction, as determined by magnetic resonance cholangiopancreatography (MRCP) or abdominal computed tomography (CT).The patients must be able to read and understand the provided informed consent form.Patients must personally sign and date the informed consent document, indicating that he/she has been informed of all pertinent aspects of the trial.Patients should be willing to comply with the scheduled visits, clinical and experimental assessment plans, and other trial procedures.

### Exclusion criteria

Patients with any clinically significant laboratory abnormalities that, in the opinion of the investigator, may increase the risk associated with trial participation or may interfere with the interpretation of the trial results.Previous history of pancreatic surgery, ESWL, or ERCP.Patients with a pancreatic stricture on cross-sectional imaging prior to study enrollment.Active alcohol or illicit drug dependency.Patients with evidence or history of medical or surgical disease of importance for this study as judged by the investigator.Patients must not have painful conditions other than CP that make them unable to distinguish the pain associated with CP from chronic pain of other origin.Presence of pancreatic head mass, multiple strictures, large ascites, and/or large fluid collections.

